If consent is provided by a representative and the patient regains the capacity to consider participation during the study period, the patient should be consulted and informed consent to continue the study obtained. If the patient refuses to give informed consent to participate they will be withdrawn from the study without compromise to their clinical care.

***3.5 Screening and eligibility assessment.*** Potential participants will be screened by the attending physicians. Screening will include clinical diagnosis and inspection of clinical notes. Results of any tests performed for clinical care during this illness episode may be used for the purposes of screening. A screening log will be kept on the ward, with a record of all patients screened and how they met/did not meet the study entry and exclusion criteria. No identifying details such as name will be recorded in this log. Patients who do not meet the study criteria will be informed as such and treated as per best available clinical care.

***3.6 Randomisation and treatment allocation.*** Randomisation will be 1:1:1:1 to the four treatment arms (intrathecal treatment and human intramuscular treatment, intrathecal treatment and equine intramuscular treatment, sham procedure and human intramuscular treatment, sham procedure and equine intramuscular treatment). Randomization will be based on a computer-based randomization list using block randomization with variable blocks lengths of 8 and 12 without stratification.

Only the study pharmacist who is not otherwise involved in the trial will have access to the randomization list and will use it to prepare treatment packages with sequential numbering. All treatment packs will be identical externally. Each patient will receive the next sequential package, which will be prepared in advance and available on the ward and stored appropriately. Each treatment pack will contain the appropriate study treatment. 

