•The attending doctors will contact the independent study doctor (see below) when a patient has entered the study. The independent study doctor who does not have normal duties on the ICU nor responsibility for day-to-day care of tetanus patients will access the treatment pack and allocation to ascertain whether the additional intrathecal injection or a sham procedure is to be performed.•The independent study doctor or a similarly independent study nurse will deliver the initial intramuscular injection of antitoxin, thus doctors and nurses treating patients will not be aware of initial intramuscular treatment.•The intrathecal injection or sham procedure will be given by the independent doctor behind screens. The sham procedure will involve placing a dressing over the lumbar area in an identical way to the procedure after true lumbar puncture. In this way doctors and nurses treating the patient will not be aware of the intrathecal treatment. Patients will be asked not to discuss their given treatment with doctors or nurses caring for them.•All patients will be kept in the supine position for 4 hours after intrathecal injection or sham procedure, in keeping with normal procedure following lumbar puncture. Supine position of tetanus patients has been shown to be non-inferior to semi-recumbent
^25^, therefore we do not think this is deleterious to patient care.•No open record of the lumbar puncture procedure or study drug administered will be kept in the clinical notes. A sealed record of the intrathecal injection procedure will be placed in a sealed envelope in the patients notes to be opened if the attending clinicians feel necessary.•Daily management decisions will be made by attending doctors (responsible for day-to-day patient care) following normal protocols and using defined criteria for mechanical ventilation.

***3.9 Baseline assessment.*** This will consist of basic clinical and demographic data, including SOFA score and Tetanus Severity Score. If a wound is present swabs will be taken for
*Clostridium tetani* culture. This will provide supportive data for the diagnosis of tetanus. Bacterial DNA may be stored for later analysis.

Cerebrospinal fluid (CSF) that has been withdrawn for antitoxin administration will be stored for analysis of tetanus toxin and antitoxin concentration.

Residual samples from these analyses may be stored for use in future studies.

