### 5 Statistics

***5.1 Sample size justification.*** Data from the Hospital for Tropical Diseases in 2013 showed that 40% of patients with tetanus required ventilation (43 out of 110 in a 6 month period). However an estimated 4–6% of patients did not have generalized tetanus and would be excluded from study entry. Therefore we estimate that 45% of study subjects without intrathecal treatment will require mechanical ventilation in our study. The main comparison of this 2x2 factorial trial is the comparison between subjects receiving intrathecal human antitoxin versus those without intrathecal treatment. To detect an absolute risk reduction for mechanical ventilation due to intrathecal treatment by 17% (from 45% to 28%) with 80% power at the two-sided 5% significance level, 250 subjects are required. To account for some protocol violations and losses to follow-up, the trial will randomize a total of 272 patients (68 in each of the four treatment arms in the 2x2 factorial trial). Should the ventilation rate in the control arm be lower than anticipated, this samples size will also detect a reduction from 40% to 24% with 80% power.

Regarding the secondary endpoint of ICU stay, median (interquartile-range) duration of ICU stay from historic data of 111 tetanus admitted to the Hospital for Tropical Diseases was 13
^4–
22^ days. Based on simulation and these historical data, 272 subjects will provide 88% power to detect a relative reduction in the ICU stay by 25% using the Cox proportional hazards model.

***5.2 Description of statistical methods.*** The primary analysis population for all analysis is the full analysis population containing all randomized patients. Patients will be analyzed according to their randomized arm (intention-to-treat). Analyses for the primary endpoint will be repeated on the per protocol population which excludes the following patients: patients not receiving the randomized intervention and other major violations of inclusion/exclusion criteria or study procedures. 

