The primary outcome measure, requirement for mechanical ventilation during ICU stay, will be summarized as x/n (%) in each group and compared between the groups based on a logistic regression model with the two interventions (intrathecal treatment vs. sham procedure, human vs equine intramuscular treatment) as the only covariates without an interaction term. The main comparison is the comparison between intrathecal treatment vs. sham procedure, but the effect of the second randomized intervention will also be summarized as a secondary comparison. As odds ratios from logistic regression are somewhat difficult to interpret for a clinical audience, we will additionally summarize relative risk reductions between the groups based on a binary regression model with a log-link rather than the logit link function used in logistic regression. Interactions between the two interventions are not expected and interaction tests will have low power but we will nevertheless assess potential interactions informally through interaction plots and formally through a likelihood ratio test for an interaction in the logistic regression model. Should the interaction test reach formal significance, we will also perform pair-wise comparisons between the 4 treatment arms.

Potential heterogeneity of the treatment effect will be assessed based on appropriate interaction (likelihood ratio) tests and the following pre-defined sub-grouping variables:

•The Tetanus Severity Score
^27^ (calculated based on information available prior to randomization only) stratified according to tertiles of the observed TSS.•Age: (≤70, 71-80, >80 years)•Pre-existing medical conditions: moderate severe illness, severe illness defined according to ASA physical state scale•Anti-toxin prior to admission

In addition, the primary endpoint will be modelled using a logistic regression model including the two interventions plus additional adjustment for the Tetanus Severity Score, age and pre-existing medical conditions.

Duration of hospital stay, duration of ICU stay, and 240 day mortality will be visualized using Kaplan-Meier curves for all 4 study arms and, additionally, for all patients with and without intrathecal treatment. Formal comparisons of these outcomes (and in-hospital mortality) will be based on Cox regression models with the two interventions as the only covariates using a similar analysis strategy as for the primary outcome described above. 

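### Efficiency, not validity: the primary model leaves out the Tetanus Severity Score, although the score is recorded at baseline and an adjusted model is already planned

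*Protocol article*

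**What the plan says.** Section 5.2 (Description of statistical methods) fixes the primary comparison as a logistic regression on the two interventions "as the only covariates without an interaction term". Later in the same section a further logistic model of the same endpoint is planned, with the two interventions "plus additional adjustment for the Tetanus Severity Score, age and pre-existing medical conditions". It is introduced as an addition to the primary model, and no reason is given for this order.

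The score is available to every analysis. Section 3.9 lists the baseline data as "including SOFA score and Tetanus Severity Score" alongside basic clinical and demographic items. The subgroup list in 5.2 restricts the score to information known before randomisation. Section 3.6 allocates patients by "block randomization with variable blocks lengths of 8 and 12 without stratification".

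Section 5.1 sizes the trial on 45% versus 28%: "with 80% power at the two-sided 5% significance level, 250 subjects are required". It raises this to 272 randomised patients and adds a fallback for a lower control rate: "this samples size will also detect a reduction from 40% to 24% with 80% power".

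**The concern.** The article itself treats severity as likely to matter. The score is the first subgroup variable and the first adjustment covariate. Yet neither the allocation nor the primary test uses it. Without stratification, the arms can differ in severity by chance, and the primary estimate takes no account of any difference that arises.

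Adjusting for a baseline variable that predicts the outcome keeps type I error and usually raises power. If the score predicts ventilation even moderately, the planned test uses less of the information in the data than the model already written beside it. What is at stake is some power, at no cost in patients or visits, in a single-hospital trial expected to recruit for three years (sections 3.1 and 12).

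**Working it through.** **1. The plan's own sample size.** Inputs from 5.1: p0 = 0.45, p1 = 0.28, two-sided 5%, 80% power, equal groups for intrathecal versus sham. With pooled variance under the null and p̄ = 0.365:

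n per group = [1.960·√(2·0.365·0.635) + 0.842·√(0.45·0.55 + 0.28·0.72)]² / 0.17²
= [1.334 + 0.564]² / 0.0289 ≈ 124.7, rounded up to 125, so 250 in total.

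This matches the article exactly. 250/0.92 ≈ 272, so the inflation is about 8%.

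**2. Power of the planned unadjusted comparison at 272 (136 per group).** The full analysis population contains all randomised patients, so 272 is the relevant number.

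- 45% versus 28%: z = (0.17·√136 − 1.334)/0.670 = 0.967, power 83.3%.
- 40% versus 24%: z = (0.16·√136 − 1.293)/0.650 = 0.882, power 81.1%.

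Both meet the stated 80%.

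**3. Power with the score added.** The article gives no figure for how well the score predicts ventilation, so this strength is an assumption, shown as a range. The simulation used 6,000 trials per setting, balanced 2×2 allocation and no effect of the intramuscular factor. The score S was standard normal, with logit P(ventilation) = a + b·S. The intercept a was solved in each arm so that the marginal rates stay at 45% and 28%. The Wald test for intrathecal versus sham was taken from the planned two-factor model and from the same model plus S. The Monte Carlo standard error is √(0.83·0.17/6000) ≈ 0.5 points.

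| Slope b | AUC (assumed) | Planned model, N = 272 | Plus score, N = 272 | Change (points) |
|---|---|---|---|---|
| 0 | 0.50 | 83.6% | 83.3% | −0.3 |
| 0.37 | 0.60 | 83.7% | 84.6% | +0.9 |
| 0.75 | 0.69 | 83.5% | 87.2% | +3.7 |
| 1.0 | 0.74 | 83.8% | 89.7% | +5.9 |
| 1.3 | 0.79 | 82.9% | 91.6% | +8.7 |
| 1.6 | 0.83 | 84.5% | 94.1% | +9.6 |

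For 40% versus 24% at 272, the change is 80.8% to 82.2% (AUC about 0.60), 80.8% to 85.2% (0.69) and 80.8% to 89.2% (0.79).

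With no treatment effect, the adjusted test rejected in 4.8% to 5.4% of trials.

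**4. The gain in patients.** The equivalent increase in sample size is [(1.96 + z_adj)/(1.96 + z_unadj)]² − 1, where z is the normal quantile of the power. At AUC 0.69 this is [(1.96 + 1.136)/(1.96 + 0.974)]² − 1 ≈ 11%. At 0.60, 0.74 and 0.79 it is about 3%, 20% and 32%.

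**5. Sensitivity to the form of the model.** With the score entered as tertiles, most of the gain remains: 86.2% at AUC 0.69 and 90.4% at 0.79. The full proposed model was also simulated at 272, with age and pre-existing conditions as covariates carrying no information. It gave about 83% versus 84%, 83% versus 87% and 83% versus 91% at slopes 0.35, 0.75 and 1.3. There was essentially no loss at slope 0, and type I error was 4% to 5%.

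**6. What changes in the estimate.** The marginal log odds ratio is ln[(0.28/0.72)/(0.45/0.55)] = −0.74. At AUC 0.69 the median unadjusted estimate is −0.74 and the median adjusted estimate −0.84. The adjusted odds ratio is conditional on the score and lies further from 1, so it answers a slightly different question.

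**The case against.** The strongest reply is that nothing in the plan is wrong. The two-factor model is a legitimate intention-to-treat analysis, the sample size was computed for an unadjusted comparison, and the trial delivers the power it states. The adjusted model is pre-specified, so the dispute is only about which of two planned analyses is called primary. All of this stands, and it is why the point concerns efficiency alone.

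The second reply is that the gain rests on an undocumented quantity. No section says how well the score predicts ventilation. Section 3.2 excludes patients already ventilated or expected to be before the injection, which narrows the range of severity. Section 2.1 leaves the final decision to ventilate to the individual doctor. Either could weaken the prediction. This also stands, and the gain must be quoted as a range that starts at zero. It does not remove the point, because adjusting for a score of no value costs almost nothing.

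The third reply is that the swap is more than a change of label. The odds ratio becomes conditional, standardisation and a missing-score rule are needed, and 5.2 analyses other binary endpoints as it does the primary one and gives the Cox models a similar strategy. These are real but small costs.

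A reader might infer that unstratified allocation biases the primary test. It does not. Chance imbalance is already covered by the test's type I error and confidence interval; adjustment only makes the estimate more precise.

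**Conclusion.** The point holds as an efficiency improvement. At 272 patients and 45% versus 28%, promoting the adjusted model changes power by about 0 to 10 points over an assumed AUC of 0.50 to 0.83, with type I error near 5%. The figures assume a fully observed score that acts linearly on the log-odds scale. The runs with tertiles and with uninformative extra covariates show that the result does not depend closely on the exact form of the model.

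A reader might also infer that the trial is short of power and needs adjustment to rescue it. The article does not support that. Section 5.1 provides for a control rate of 40%, and its claim of 80% power there recomputes to 81.1%. Lower figures need a further assumption that the article does not make. One example is that the planned relative reduction (28/45) carries over unchanged to a 40% control rate, which gives about 76%. Nor can it be said that power is certainly lost, since that depends on how well the score predicts ventilation.

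**What to change.** Before unblinding:

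- Make the adjusted logistic model the primary analysis of the primary endpoint: both interventions plus the Tetanus Severity Score as a continuous term, age and pre-existing conditions. Use the version of the score limited to pre-randomisation information, as the subgroup list already requires.
- Report the standardised (marginal) risk difference and risk ratio from this model beside the conditional odds ratio. This also serves the article's stated wish for a measure that clinicians can read more easily than an odds ratio.
- Fix a rule for patients with a missing score, so that all randomised patients stay in the analysis.
- Keep the two-factor model as the supportive analysis.
- State whether the change extends to the other endpoints that follow the primary method or is confined to the primary endpoint.

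The cost is a conditional odds ratio, a standardisation step and an amendment to the protocol and analysis plan. If the amendment counts as substantial, section 8.2 requires approval from the ethics bodies named there. No extra data, visits or patients are needed.

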***1.2 Secondary objectives***

•To determine whether the addition or intrathecal tetanus antitoxin reduces autonomic nervous system dysfunction and length of hospital/ICU stay.•To establish whether the addition of intrathecal tetanus antitoxin in the form of Tetagam-P is safe and cost-effective.•To provide data to inform the recommendation of human rather than equine antitoxin

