***2.2 Secondary End Points***

•Duration of ICU stay•Duration of hospital stay•Duration of mechanical ventilation•In hospital and 240-day mortality and disability•New antibiotic prescription during ICU stay (excluding antibiotics for tetanus or initial entry site infection)•Incidence of Ventilator Associated Pneumonia•Incidence of the clinical syndrome of autonomic nervous system dysfunction•Total dose of benzodiazepines and pipecuronium during hospital stay•Incidence of adverse events

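### Cox regression for in-hospital mortality can show a hazard ratio above 1 merely because treated survivors go home sooner; a binary analysis avoids this

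*Protocol article*

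**What the plan says.** Section 2.2 of the protocol article lists durations of ICU and hospital stay as secondary endpoints, together with "In hospital and 240-day mortality and disability". Section 5.2 sets the display: "Duration of hospital stay, duration of ICU stay, and 240 day mortality will be visualized using Kaplan-Meier curves for all 4 study arms". It then sets the model: "Formal comparisons of these outcomes (and in-hospital mortality) will be based on Cox regression models with the two interventions as the only covariates".

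The same section gives the primary endpoint a logistic model plus a binary regression with log link, and sends other binary endpoints down that route. In-hospital mortality is taken out of that group and given to Cox regression.

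Section 1.2 makes it an objective to learn whether intrathecal antitoxin "reduces autonomic nervous system dysfunction and length of hospital/ICU stay". Section 5.1 adds that "272 subjects will provide 88% power to detect a relative reduction in the ICU stay by 25% using the Cox proportional hazards model". Section 2 follows patients for death after discharge, to day 240.

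The article does not say whether patients discharged alive are censored or kept at risk in the in-hospital mortality model. It does not say how a death counts in a length of stay. It names no competing-risk method.

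**The concern.** Every patient leaves hospital alive or dead, so in-hospital death is a complete yes/no outcome and its timing is not needed to compare risks. A Cox model brings timing back in. If survivors are censored at discharge, the death hazard on a given day is the deaths that day divided by the patients still in hospital. Treatment is hoped to shrink that denominator. The same number of deaths over fewer remaining patients gives a higher hazard, so the effect the trial hopes for would appear as excess in-hospital mortality.

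Safety of an added lumbar injection is a stated objective, and a hazard ratio above 1 for in-hospital death would be read in that light. A real reduction in deaths could also be masked.

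Length of stay raises a related, smaller question. If death counts as the end of a stay, an early death looks like a quick discharge.

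**Working it through.** **The plan's own Cox figure.** The only stated figure that uses this method is the 88% power for ICU stay. Its historical input is given as "median (interquartile-range) duration of ICU stay from historic data of 111 tetanus admitted to the Hospital for Tropical Diseases was 13" days, with quartiles read as 4 and 22. A Weibull shape from the upper quartile and median is ln 2 / ln(22/13) = 1.32. Then HR = (1/0.75)^1.32 = 1.462 and power = Φ(√(272/4) × ln 1.462 − 1.96) = Φ(3.13 − 1.96) = 0.88. Other shapes give 58% to 97%. The figure rests on historical data that are not shown, so it cannot be reproduced uniquely, but it is attainable and nothing here shows it to be wrong.

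**Why the hazard ratio moves.** Write f(t) for the rate at which in-hospital deaths occur among all randomised patients, and S(t) for the proportion still in hospital. The discharge-censored hazard of death is f(t)/S(t). If both arms have the same f(t), the hazard ratio at time t is S_control(t)/S_treated(t), which exceeds 1 wherever treated patients have left sooner.

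**Assumed inputs** (not in the documents, which only call mortality low):
- in-hospital death risk 5% in both arms;
- time to death gamma with shape 1.5, mean 12 days (scale 8);
- time to discharge log-normal, median 22 days, sigma 0.6;
- treated discharge times multiplied by 0.75. The 25% is the protocol's own effect size for ICU stay, applied here to hospital discharge.

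**By hand**, with S(t) = 0.95 × P(discharge > t) + 0.05 × P(death > t):

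| Day | Control S | Treated S | Ratio |
|---|---|---|---|
| 3 | 0.95 × 0.9996 + 0.05 × 0.861 = 0.993 | 0.95 × 0.9978 + 0.05 × 0.861 = 0.991 | 1.00 |
| 12 | 0.95 × 0.844 + 0.05 × 0.392 = 0.821 | 0.95 × 0.702 + 0.05 × 0.392 = 0.687 | 1.20 |
| 21 | 0.95 × 0.531 + 0.05 × 0.154 = 0.512 | 0.95 × 0.344 + 0.05 × 0.154 = 0.334 | 1.53 |

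The Cox estimate averages such ratios over the days on which deaths occur, so the timing of deaths governs the result.

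**Large-sample simulation, true risk ratio 1.00, discharge 25% faster:**

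| Assumed mean time to death | Discharge-censored Cox HR |
|---|---|
| 3 days | 1.02 |
| 6 days | 1.06 |
| 12 days | 1.20 to 1.22 (repeat runs) |
| 21 days | 1.44 |

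Keeping discharged patients in the risk set returns 0.99 to 1.00 in all four rows. With the 12-day mean and all times, including times to death, shortened by 25%, the ratio is about 1.19.

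**A second set of assumptions.** With Weibull stays (shape 1.32, median 13 days), control-arm deaths on the same time scale and only discharge speeded, the ratio is 1.52, 1.47 and 1.36 at 5%, 10% and 20% mortality. Low mortality does not remove the effect, because discharge drives it. At 272 patients, equal mortality is rejected in about 10%, 14% and 20% of trials, against 3%, 4% and 5% with discharged patients kept at risk.

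**A real benefit.** If deaths fall from 10% to 8% (risk ratio 0.80) while discharge is 25% faster, discharge-censored Cox gives about 0.95 under the first set (12-day mean) and 1.16 under the second.

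**Length of stay.** Assume no effect on survivors' discharge and early deaths (median day 4). With 20% against 10% deaths and death counted as end of stay, the arm with more deaths has HR 1.09 for leaving and a median stay of 10.2 against 11.7 days. Counting deaths as never discharged alive gives 0.77. At 10% against 5%, the two codings give 1.04 and 0.86.

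**The case against.** **The text names a model, not a censoring rule.** Deaths after discharge are observed to day 240, so discharged patients could stay in the risk set, and that coding gives a ratio near 1. A journal article may leave such coding to the analysis plan. This stands. A reader might infer that the plan must censor at discharge and so must be biased; the document does not say that. What remains is that it chooses a time-to-event model for a complete binary outcome, and the usual coding of that model misleads under the hoped-for effect.

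**The size rests on unknown inputs.** This also stands: if patients die early, the ratio hardly moves. At 5% mortality there would be about 0.05 × 272 = 14 deaths. Under the first set of assumptions with the 12-day mean, the rejection rate at 272 patients is 6.4%, against 4.7% with no discharge effect.

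**A cause-specific hazard ratio is legitimate.** True, but it does not measure the risk of dying in hospital, which is how an in-hospital mortality comparison will be read.

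**Other results would sit beside it.** 240-day mortality is followed past discharge and is free of the problem. Following the primary endpoint's strategy would plausibly also put death counts next to the hazard ratio.

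**Length of stay.** A reader might infer that Cox or Kaplan-Meier forces a choice between death as end of stay and death as censoring. It does not: deaths can be kept in the risk set, or censored at the longest observed stay, within the planned framework. This is an unstated coding rather than a stated error.

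**Conclusion.** The point holds for in-hospital mortality. Section 5.2 fixes a model whose usual coding yields a ratio above 1 when treatment speeds discharge and death risk is equal. Under the first set of assumptions the ratio runs from about 1.02 to 1.44 for mean times to death of 3 to 21 days, and other assumed stays reach 1.52. The direction was the same in every equal-risk scenario tried. The size cannot be fixed from the documents, which give no in-hospital mortality rate, times to death or hospital stay distribution.

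For length of stay the point is a request to state the coding. The distortion from counting death as end of stay is small if mortality is low and balanced.

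Severity is moderate. The primary endpoint, its model and its sample size are untouched, and Cox regression for 240-day mortality is sound on this point. The documents do not support reading this as a flaw in the trial's main conclusion.

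**What to change.** 1. In section 5.2, remove in-hospital mortality from the Cox sentence. Analyse it as a binary outcome with the logistic and log-link models already used for the primary and other binary endpoints, and report deaths over patients randomised in each arm.
2. Keep Cox regression for 240-day mortality.
3. Define ICU and hospital stay as time to discharge alive, with death as a competing event. Show cumulative incidence of discharge alive, and state how deaths enter the model, for example kept in the risk set (Fine-Gray) or censored at the longest observed stay.

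The cost is wording; no new data are needed. One consequence of the third change should be checked. With stays 25% shorter for survivors and equal mortality, under the Weibull assumptions above, keeping deaths in the risk set lowers the hazard ratio for discharge from 1.43 to 1.30 at 5% mortality, and from 1.39 to 1.23 at 10%. The 88% power statement should therefore be rechecked under whichever coding is chosen.

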Other binary endpoints will be analysed in the same way as for the primary outcome. In addition, the rate of new antibiotics prescriptions, ventilator associated pneumonia and other predefined HAI, and the clinical syndrome of autonomic nervous system dysfunction will be modelled with a Poisson-regression model with the log-transformed duration of ICU stay included as an offset.

The cost–effectiveness analysis will be performed from the healthcare provider perspective, thus including direct costs resulting from the implementation of the intervention in the ICU and subsequent costs during the hospital stay, as well as any costs associated with re-admission during the 240 day follow-up. This will include the costs for standard tetanus treatment, the incremental cost of intrathecal human antitoxin administration, and those for any other diagnostics and treatments provided during ICU admission, including time spent on mechanical ventilation.

Prospectively collected data entered in the Case Report Forms from all patients included in the trial will be used for the cost analyses. The unit costs of intrathecal human antitoxin administration and those for mechanical ventilation will be estimated using a detailed micro costing approach. The cost per day of mechanical ventilation will account for the annualized cost of the equipment, maintenance, consumables and staff time.

If the intervention does improve patient survival at a higher cost, we will calculate the incremental cost per ICU survivor. This will be extended to estimating the cost per quality adjusted life year (QALY) gained using the survival data at 240-day-after enrolment follow-up and modelling the anticipated QALYs gained for these patients based on life expectancy and QALYs gained in ICU survivors in the region.

Statistical analysis will be carried out using the latest version of R.

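### The added Poisson rate model offsets by ICU stay, itself a trial outcome, and the plan does not say whether it or the per-patient analysis leads when the two disagree

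*Protocol article*

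**What the plan says.** Section 2.2 lists among the secondary end points "New antibiotic prescription during ICU stay", "Incidence of Ventilator Associated Pneumonia" and "Incidence of the clinical syndrome of autonomic nervous system dysfunction". Duration of ICU stay is on the same list. The first secondary objective (section 1.2) asks whether adding "intrathecal tetanus antitoxin reduces autonomic nervous system dysfunction and length of hospital/ICU stay", so autonomic dysfunction and ICU stay stand side by side as things the treatment may improve. Section 5.1 gives ICU stay its own power statement: "272 subjects will provide 88% power to detect a relative reduction in the ICU stay by 25" per cent.

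Section 5.2 then plans two analyses for these complications. The first is per randomised patient: "Other binary endpoints will be analysed in the same way as for the primary outcome", that is, a logistic model and a log-link model with the two interventions as covariates and no offset. The second follows at once: "In addition, the rate of new antibiotics prescriptions, ventilator associated pneumonia and other predefined HAI", together with autonomic dysfunction, "will be modelled with a Poisson-regression model with the log-transformed duration of ICU stay included as an offset". No order of precedence is given. Other predefined hospital-acquired infection is named only in the second sentence, although it may fall under the first as another binary endpoint.

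**The concern.** An offset of log ICU days turns the comparison into events per ICU-day. That is harmless when the exposure time is unaffected by treatment. Here the exposure time is an outcome that the trial sets out to change. A shorter stay under intrathecal treatment shrinks the denominator in that arm and pushes the rate ratio up, whatever happens to the number of complications. If complications also lengthen stay, the numerator drives its own denominator.

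The denominator is also a loose measure of time at risk. VAP can arise only on ventilated days, and ventilation is the primary end point, expected to differ between arms. If autonomic dysfunction is counted once per patient, as the word incidence suggests, the ICU days after onset are not exposure.

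What is at stake is how the secondary results read. A formal treatment comparison could show no effect, or apparent harm, on outcomes where fewer patients are affected, next to another formal comparison that shows benefit, with no rule for choosing between them.

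**Working it through.** **Inputs.** From section 5.1: a 25% relative reduction in ICU stay; historic median stay 13 days, with interquartile range read as 4 to 22; ventilation 45% versus 28%; 272 patients, so 136 versus 136 for the intrathecal comparison. The article gives no event risk for these complications. Where one is needed it is an assumption: 40% in controls unless stated.

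**The plan's own figures.** The article gives no figure for the offset model, so only its inputs can be checked.
- Sample size for 45% versus 28% (two-sided 5%, 80% power): n per group = [1.96·√(2·0.365·0.635) + 0.842·√(0.45·0.55 + 0.28·0.72)]² / 0.17² = 125, or 250 in total, as stated.
- ICU-stay power: a Weibull distribution fitted to median 13 and upper quartile 22 has shape ln(ln 4/ln 2)/ln(22/13) = 1.32. A 25% shorter stay is then a hazard ratio of (1/0.75)^1.32 = 1.46. With 272 events, power = Φ(√(272/4)·ln 1.46 − 1.96) = about 88%, as stated. Other shapes give less (66% if exponential), but the plan used simulation on data not shown, so its 88% is not shown to be wrong.

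**What the offset does.** With treatment as covariate, the fitted ratio is total events over total ICU days in one arm divided by the same in the other. With equal arms:

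rate ratio = (ratio of events per patient) / (ratio of mean ICU stay).

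| True ratio of events per patient | Stay 15% shorter | Stay 25% shorter | Stay 35% shorter |
|---|---|---|---|
| 1.00 | 1.18 | 1.33 | 1.54 |
| 0.85 | 1.00 | 1.13 | 1.31 |
| 0.75 | 0.88 | 1.00 | 1.15 |
| 0.60 | 0.71 | 0.80 | 0.92 |

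The first column is what the analysis without offset estimates on the risk-ratio scale. With stay unchanged, both analyses give the same ratio.

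**VAP.** If ventilation falls from 45% to 28% and the VAP risk per ventilated patient is unchanged, VAP per randomised patient falls to 28/45 = 0.62. With stay 25% shorter, the rate per ICU-day falls only to 0.62/0.75 = 0.83.

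**Simulation** (272 patients, the Weibull stay above, 25% shorter under treatment, once-per-patient events with risk unrelated to stay):
- True ratio 0.85: offset model 1.13.
- True ratio 0.75: offset model 1.00. It reaches significance in about 3% of trials, against 40% for the logistic model.
- True ratio 0.60: offset model 0.79. It reaches significance in about 16% of trials, against 80% for the logistic model.
- True ratio 1.00: the offset model declares significant harm in roughly 30% of trials (about 17% at an assumed 20% risk, about 43% at 60%).
- Stay unchanged and true ratio 0.85: offset model 0.85.

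**Time at risk.** With the same constant daily hazard in both arms (assumed 0.03 per day) and stay 25% shorter, counts of repeat events give a rate ratio of 1.00, the right answer for a daily rate. If only the first event counts, the same model gives 1.07, because days after the event are still counted as exposure.

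**The case against.** The strongest reply is that the per-patient analysis is already planned and comes first; the rate model is introduced as an addition. That stands. A reader might infer that the planned analysis as a whole would lose or reverse a real benefit. The article does not support that, because the logistic and log-link comparison has no offset and would still show it.

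Second, events per ICU-day is a legitimate quantity. If patients have fewer complications only because they leave sooner, a ratio of 1 is the correct answer to the daily-rate question. This also stands, but it is a different question from the incidence that section 2.2 lists. Whole-stay ICU days answer it poorly for VAP and for a first-event outcome.

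Third, the 25% in section 5.1 is an effect the trial is powered to detect under a Cox model, not a forecast of the fall in mean ICU-days. The figures are therefore conditional, and the table shows how they move.

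Fourth, a reader might infer that the Poisson standard errors are wrong: too narrow for clustered repeat events, too wide for once-per-patient events. The article names no variance estimator and may leave it to the statistical analysis plan, so this is not an error in the text. How autonomic episodes are counted is likewise not stated.

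Finally, counts per patient have a weakness of their own: someone who dies early has little time to acquire an infection. The Discussion says mortality in the unit is low, which limits this, and it is a fair reason to keep rates as a supplement.

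**Conclusion.** The concern holds for the added rate analysis, not for the whole plan. The offset is a post-randomisation end point that the trial hopes to shorten, so the rate ratio cannot be read as the effect on complications. At a 25% fall in mean stay, the distortion is a factor of 1/0.75 = 1.33. That is enough to turn a 25% reduction in events per patient into no effect, and a 15% reduction into apparent harm of 1.13. These ratios assume that mean stay falls by that amount; they do not depend on the event risk, whereas the simulated rejection rates do. If stay does not change, the problem disappears.

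What remains is a gap in precedence. Two formal comparisons of the same secondary outcomes can disagree in direction exactly when treatment shortens stay, and the article does not say which one counts. The primary end point is unaffected.

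**What to change.** State in section 5.2 that conclusions about treatment effect on these outcomes rest on the analysis per randomised patient without offset:
- for any event, the logistic and log-link models already planned, naming other predefined hospital-acquired infection explicitly;
- for repeat events, the number per patient during the ICU stay, with robust or negative-binomial standard errors.

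Keep any rate per exposure as a descriptive supplement, labelled as not a randomised comparison, and express VAP per ventilator-day rather than per ICU-day.

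Keep the counting window at the ICU stay. Section 3.10 describes recording infections and new antibiotics while the patient is in ICU, so a window covering the hospital stay or a fixed period from randomisation might need data that are not shown to be collected.

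The change is wording only. Ventilator-days need nothing new, because daily interventions are recorded and duration of ventilation is already an end point. The cost is that the plan gives up a formal test of the rate per ICU-day. The change should be made before unblinding, so that the choice cannot look driven by the results.
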